### Recruitment

All patients will be recruited from three hospitals in the North Wales Cancer Network: Ysbyty Gwynedd, Ysbyty Glan Clwyd, and Ysbyty Maelor. The research nurse and three clinical nurse specialists (CNSs) will identify women from the hospital databases, in line with the inclusion and exclusion criteria above. Eligible patients will be approached by the clinic medical team and/or by the research nurse/CNS and will be invited to take part in the study. Patients will be given a participant information sheet at their end-of-treatment visit and will have until their follow-up appointment to consider the study (usually around 6 weeks), and those who would like to participate will have the opportunity to contact the research nurse by phone or email for more information before their follow-up appointment. Patients will be informed that if they agree to participate, they will be randomly assigned to one of the two treatment groups, both receiving slightly different modes of follow-up support. After agreeing to take part in the study, patients will give written consent at their 3-month routine follow-up appointment.

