### Purpose and scope

This study will evaluate the feasibility of a nurse-led needs assessment in the gynaecology cancer setting in North Wales and its utility to health care professionals when making decisions about supportive care, compared to disease- and site-matched patients not receiving the nurse-led needs assessment. The nurse-led intervention will be known as Optimal Personalised Care After Treatment for Gynaecological cancer (OPCAT-G) and will comprise patient education, patient empowerment and protocol-based, structured needs assessment undertaken with Gynae Oncology clinical nurse specialists (CNSs) by telephone. Patients will receive an initial structured telephone interview with a gynaecological CNS and a booklet including information on symptoms of recurrence and possible long-term physical and psychological side-effects of treatment. Information will also be given to patients on how they can contact the clinical team if they have concerns or symptoms; otherwise, they will receive routine telephone contact 6 months later. The telephone follow-up will involve a structured interview whereby patients’ unmet needs will be identified and patients will receive appropriate referral(s). The new approach will maintain regular contact with patients but will not involve routine hospital, outpatient attendance. The aim of this follow-up programme is to manage any long-term effects from treatment, to reassure the patient that the cancer remains in remission and if relapse occurs, to detect and treat it early.

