### Standard care

After patients have been allocated to the standard care arm of the study, they will be informed about the next part of the study and their 6- and 9-month appointments scheduled. Patients randomised to standard care will continue to have their usual hospital-based doctor-led medical reviews (at 6 and 9 months post-treatment conclusion) and will be followed up according to an agreed protocol with the regional gynaecological cancer MDT and representing current practice. This will include an agreed protocol on further blood tests and scans if considered appropriate to routine follow-up.

In addition to their usual follow-up appointments, patients will be asked to complete a set of outcome questionnaires at baseline (following consent, but prior to randomisation), with assistance from the research nurse or CNS at the 3-month follow-up appointment. Patients will then be asked to complete the same set of outcome measures at the end of each of their follow-up appointments. If this is not possible, then the research nurse will send the questionnaires by post for completion and return in a self-addressed, pre-stamped envelope.

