### Nurse-led intervention

Patients in the intervention group will not attend the hospital for their usual follow-up appointments but will receive a nurse-led telephone follow-up intervention, known as Optimal Personalised Care After Treatment for Gynaecological cancer (OPCAT-G). After patients have been allocated to the nurse-led intervention arm of the study, the research nurse or CNS will inform patients of their allocation. The CNS will give the patients an information booklet at the end of their 3-month medical review and will guide the patient through the sections of the booklet. The information booklet will include information on patterns of relapse, possible warning symptoms and how to respond to these. Information will also be given on possible long-term physical and psychological side-effects of treatment and how these can be managed. Information will also be given to patients on how they can contact the clinical team if they have concerns or symptoms. Patients will receive treatment and diagnosis-specific supplementary leaflets attached to the booklet. The CNS will also give patients a set of needs assessment measures, including:Macmillan Concerns Checklist [37]The Macmillan Concerns Checklist addresses 23 physical concerns; 9 practical concerns; 3 family/relationship concerns; 9 emotional concerns; 3 spiritual or religious concerns; and 9 lifestyle or information needs. Patients are asked to tick a box for any problems that have caused concern during the previous week or to leave the box blank if it does not apply to them.CancerCAN-22 [24, 38, 39]This is a multi-domain needs assessment tool that measures unmet needs across 22 items (12 psychosocial needs items and 10 treatment and care items). Items are either met, unmet or never had/not applicable; then scored for salience if unmet on a 0–3 Likert scale (no importance, low importance, medium importance and high importance).Distress thermometerThis is a reliable measure of patients’ distress and concerns and is widely used in cancer studies [40]. It has accepted cut-offs indicative of clinical levels of global distress.

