Patients will be asked to complete the needs assessment measures prior to a scheduled telephone call from the CNS. Patients will receive a scheduled telephone call within 4 weeks of randomisation and will be notified of their scheduled telephone call date and time at the end of their 3-month medical review. Patients will also receive a letter confirming the date and time of their scheduled telephone call.

The scheduled telephone call will involve a structured interview with the CNS. Patients will be asked about their general wellbeing and about any gynaecological symptoms experienced. Any identified needs or concerns from the three needs assessment measures will be discussed. Patients in whom problems or unmet needs are identified will be evaluated and directed to the most appropriate source of help. This could include a patient self-help group, their general practitioner, or hospital review by the gynaecology, oncology or clinical psychology team. These additional appointments would be facilitated by the CNS who would ensure appropriate communication regarding the reasons for referral. This information, including advice and follow-up suggestions, will be recorded using a case note sheet. Patients referred for further hospital review will be discharged to continue telephone review once their immediate problem has been assessed and treated or resolved. Patients will receive additional copies of the needs assessment measures by post. Patients will be told that if they have any problems between telephone calls, they should complete their assessments and contact the CNS. Patients will be encouraged to report problems promptly with these concerns addressed in the same structured way.

Patients will then receive another scheduled telephone call at 9 months post-treatment. Patients will receive a letter confirming the date and time of their telephone call appointment by post. Patients will also receive the three needs assessment measures by post and will be asked to complete them prior to their scheduled telephone call from the nurse. The telephone contact will again include a structured interview and any identified needs or concerns will be discussed following the same structure of the first telephone call interview.

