In addition to the nurse-led intervention, patients will be asked to complete the same set of outcome questionnaires as patients in the standard care arm. The outcome questionnaires will be completed at baseline (prior to randomisation) with assistance from the research nurse or CNS at the 3-month follow-up appointment. Patients will receive the same set of outcome questionnaires by post at 6 months post-treatment and within a week of their 9-month telephone follow-up and will be asked to return them in a self-addressed, pre-stamped envelope.

For this study, we will consider the study endpoint to be the 9 months post-treatment data collection. After the 9-month data collection point, the intervention and control arm patients will continue with follow-up care as the clinician advises and is available to the local service.

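### The Recruitment section's wording on what women are told about the two arms understates the contrast under test and should be aligned with the design (minor, cheap to fix)

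*Protocol article*

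**What the plan says.** The Recruitment section sets out what patients will be told when invited: that they will be allocated at random to one of two groups, "both receiving slightly different modes of follow-up support". It also says that they receive a participant information sheet at the end-of-treatment visit, usually have around six weeks to consider it, and can contact the research nurse with questions. Written consent is taken at the 3-month appointment.

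The arms are described in three other places.

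- Purpose and scope: the new approach keeps contact with patients but "will not involve routine hospital, outpatient attendance".
- Nurse-led intervention: "Patients in the intervention group will not attend the hospital for their usual follow-up appointments but will receive a nurse-led telephone follow-up intervention". Calls are scheduled within 4 weeks of randomisation and at 9 months post-treatment. Where a call identifies a problem, the nurse can direct the patient to several sources of help, including "hospital review by the gynaecology, oncology or clinical psychology team".
- Standard care: patients keep doctor-led hospital reviews at 6 and 9 months, with an agreed protocol for blood tests and scans where appropriate.

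The Nurse-led intervention section adds that, after the 9-month data collection, "the intervention and control arm patients will continue with follow-up care as the clinician advises".

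Under Primary outcome measures, the recruitment rate is written consents relative to eligible patients invited. Under Statistical methods, a full trial is considered feasible if recruitment is at least 50% and retention no less than 50%. The Design section lists acceptability of randomisation among the purposes of the study.

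**The concern.** The adverb in the Recruitment section does not fit the design. During the trial the arms differ in where follow-up takes place (hospital or telephone), who provides it (doctor or nurse) and whether routine in-person review happens at all. The Aim section names exactly this contrast as the comparison that a full trial would test.

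In many trials such a phrase would be loose prose with no statistical consequence. Here consent is itself a primary outcome, and the feasibility decision depends partly on it. A recruitment rate is useful for planning a full trial only if the women who said yes or no were responding to the contrast that the full trial would offer. If they were responding to a milder description, the rate answers a different question.

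**Working it through.** **1. The description beside the design**

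| Feature, after randomisation and up to 9 months | Standard care | Intervention |
|---|---|---|
| Scheduled review | Hospital, at 6 and 9 months | Telephone, within 4 weeks of randomisation and at 9 months |
| Who reviews | Doctor | Clinical nurse specialist |
| Routine hospital attendance | Yes | None |
| Hospital review on need | Not at issue | On referral from the nurse |
| At 6 months | Hospital review and questionnaires | Questionnaires by post |

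Both arms have the 3-month hospital review, because randomisation takes place at its end. After 9 months both arms follow clinical advice. The difference is therefore confined to the reviews after randomisation and up to 9 months, but within that window it is the whole of the trial contrast. The phrase in the Recruitment section does say that the modes of follow-up differ; the fault is one of degree.

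**2. The plan's own recruitment figure**

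Inputs from the Sample size section: throughput about 150, 30% ineligible, 50% acceptance assumed.

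- Eligible: 150 × (1 − 0.30) = 105
- Consenting: 105 × 0.50 = 52.5, in line with the rounded target of 50

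**3. Where the threshold falls**

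Assume that all 105 eligible women are invited.

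- 53/105 = 50.5%, which meets the 50% criterion
- 52/105 = 49.5%, which does not

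Planned acceptance and the threshold are the same number, so the criterion is sensitive to any shift in uptake, whatever its cause. With X binomial (105, p), the chance of passing is P(X ≥ 53):

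| True consent rate p (assumed) | P(pass) |
|---|---|
| 40% | 0.02 |
| 45% | 0.15 |
| 50% | 0.50 |
| 55% | 0.85 |
| 60% | 0.98 |

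This table describes the threshold and is not an estimate of a wording effect. The documents contain nothing from which such an effect could be derived. If the wording makes no difference to consent, nothing in the table changes.

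**4. Whether the other primary outcome would reveal a problem**

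The Randomisation section places baseline questionnaires after consent and before allocation. The attrition rate compares those who consented with those who completed any measures. Read literally, a woman who completes baseline and withdraws on learning her allocation counts as both recruited and retained. The attrition rate therefore cannot be relied on to show whether women were surprised by what their arm involved.

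**The case against.** The strongest objection is that the quoted clause is the article's own summary and not a script. The description that women rely on would be the participant information sheet, which is not shown. They have usually about six weeks with it and can ask questions. The Trial management plan also provides for patient representatives to contribute to the information and consent materials. This stands: the sheet may describe the arms in full, in which case only the article's sentence needs correcting.

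Two stronger readings are tempting, and the documents support neither.

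- *A reader might infer that the recruitment rate will overstate willingness to be randomised.* The direction is not established. The Background says that hospital follow-up leaves many needs unaddressed and mentions time off work and childcare, so a fuller account of telephone follow-up could raise consent as well as lower it.
- *A reader might infer that informed consent is deficient.* That cannot be judged without the information sheet and consent form, and their absence here is no evidence against the plan.

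It is also fair that the intervention does not remove access to hospital care: referral remains possible, and patients are told how to contact the team. Entry is limited to women whose consultant sees no definite need for continued hospital-based care. These facts limit the contrast, but they do not make the loss of the scheduled reviews slight. Finally, the plan already logs how many patients are offered the study and asks those who decline for their reasons, so that safeguard need not be added.

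What survives is narrower: the plan says patients will be informed in these terms, and the terms do not match its own description of the arms.

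**Conclusion.** The point holds as a minor one. The sentence on what women will be told understates the design and should be reconciled with the Purpose and scope, Standard care and Nurse-led intervention sections. If women are told only this, the recruitment rate may not measure willingness to be randomised between the arms as delivered. That matters somewhat more than usual because consent is a primary outcome and planned acceptance equals the 50% threshold, so one consent in 105 can separate a pass from a fail.

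The size and direction of any effect on consent are unknown, and no corrected recruitment figure can be given. The counts assume a throughput of 150, 30% ineligible and every eligible woman invited; the pass probabilities also assume independent decisions with a common consent rate. The conclusion is conditional on the patient materials repeating the article's wording, which cannot be checked from the document at hand.

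**What to change.** In the Recruitment section, replace the phrase with the contrast as the protocol already defines it: one group keeps doctor-led hospital reviews at 6 and 9 months; the other has no routine hospital attendance in that period and is followed by nurse telephone calls, with hospital review on referral. Then confirm that the invitation and the participant information sheet give the same description at all three hospitals, since the approach may be made by the clinic team, the research nurse or a clinical nurse specialist. If the sheet already does so, only the protocol sentence changes.

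The cost is a wording amendment, extended to patient materials only if they need it. The recruitment rate may change in either direction, but it would then refer to the comparison that a full trial would offer.

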### Randomisation

Following their 3-month appointment, consenting patients will complete the baseline measures (see below) then be randomised at the end of the 3-month review appointment. Patients will be randomised on a 1:1 ratio by the North Wales Organisation for Randomised Trials in Health (NWORTH) using a dynamic, independent, secure, web-based, randomisation procedure that can be accessed 24 h a day [36]. Patients will be randomised to one of the two arms of the study: standard care or nurse-led intervention. Site and disease type will be included as stratification variables. The participants, research nurse, CNSs and trial management will be unblinded during this trial. All other members of the team, especially the trial statistician, will remain blinded.

### Standard care

After patients have been allocated to the standard care arm of the study, they will be informed about the next part of the study and their 6- and 9-month appointments scheduled. Patients randomised to standard care will continue to have their usual hospital-based doctor-led medical reviews (at 6 and 9 months post-treatment conclusion) and will be followed up according to an agreed protocol with the regional gynaecological cancer MDT and representing current practice. This will include an agreed protocol on further blood tests and scans if considered appropriate to routine follow-up.

In addition to their usual follow-up appointments, patients will be asked to complete a set of outcome questionnaires at baseline (following consent, but prior to randomisation), with assistance from the research nurse or CNS at the 3-month follow-up appointment. Patients will then be asked to complete the same set of outcome measures at the end of each of their follow-up appointments. If this is not possible, then the research nurse will send the questionnaires by post for completion and return in a self-addressed, pre-stamped envelope.

### Nurse-led intervention

Patients in the intervention group will not attend the hospital for their usual follow-up appointments but will receive a nurse-led telephone follow-up intervention, known as Optimal Personalised Care After Treatment for Gynaecological cancer (OPCAT-G). After patients have been allocated to the nurse-led intervention arm of the study, the research nurse or CNS will inform patients of their allocation. The CNS will give the patients an information booklet at the end of their 3-month medical review and will guide the patient through the sections of the booklet. The information booklet will include information on patterns of relapse, possible warning symptoms and how to respond to these. Information will also be given on possible long-term physical and psychological side-effects of treatment and how these can be managed. Information will also be given to patients on how they can contact the clinical team if they have concerns or symptoms. Patients will receive treatment and diagnosis-specific supplementary leaflets attached to the booklet. The CNS will also give patients a set of needs assessment measures, including:Macmillan Concerns Checklist [37]The Macmillan Concerns Checklist addresses 23 physical concerns; 9 practical concerns; 3 family/relationship concerns; 9 emotional concerns; 3 spiritual or religious concerns; and 9 lifestyle or information needs. Patients are asked to tick a box for any problems that have caused concern during the previous week or to leave the box blank if it does not apply to them.CancerCAN-22 [24, 38, 39]This is a multi-domain needs assessment tool that measures unmet needs across 22 items (12 psychosocial needs items and 10 treatment and care items). Items are either met, unmet or never had/not applicable; then scored for salience if unmet on a 0–3 Likert scale (no importance, low importance, medium importance and high importance).Distress thermometerThis is a reliable measure of patients’ distress and concerns and is widely used in cancer studies [40]. It has accepted cut-offs indicative of clinical levels of global distress.

Patients will be asked to complete the needs assessment measures prior to a scheduled telephone call from the CNS. Patients will receive a scheduled telephone call within 4 weeks of randomisation and will be notified of their scheduled telephone call date and time at the end of their 3-month medical review. Patients will also receive a letter confirming the date and time of their scheduled telephone call.

The scheduled telephone call will involve a structured interview with the CNS. Patients will be asked about their general wellbeing and about any gynaecological symptoms experienced. Any identified needs or concerns from the three needs assessment measures will be discussed. Patients in whom problems or unmet needs are identified will be evaluated and directed to the most appropriate source of help. This could include a patient self-help group, their general practitioner, or hospital review by the gynaecology, oncology or clinical psychology team. These additional appointments would be facilitated by the CNS who would ensure appropriate communication regarding the reasons for referral. This information, including advice and follow-up suggestions, will be recorded using a case note sheet. Patients referred for further hospital review will be discharged to continue telephone review once their immediate problem has been assessed and treated or resolved. Patients will receive additional copies of the needs assessment measures by post. Patients will be told that if they have any problems between telephone calls, they should complete their assessments and contact the CNS. Patients will be encouraged to report problems promptly with these concerns addressed in the same structured way.

Patients will then receive another scheduled telephone call at 9 months post-treatment. Patients will receive a letter confirming the date and time of their telephone call appointment by post. Patients will also receive the three needs assessment measures by post and will be asked to complete them prior to their scheduled telephone call from the nurse. The telephone contact will again include a structured interview and any identified needs or concerns will be discussed following the same structure of the first telephone call interview.

In addition to the nurse-led intervention, patients will be asked to complete the same set of outcome questionnaires as patients in the standard care arm. The outcome questionnaires will be completed at baseline (prior to randomisation) with assistance from the research nurse or CNS at the 3-month follow-up appointment. Patients will receive the same set of outcome questionnaires by post at 6 months post-treatment and within a week of their 9-month telephone follow-up and will be asked to return them in a self-addressed, pre-stamped envelope.

For this study, we will consider the study endpoint to be the 9 months post-treatment data collection. After the 9-month data collection point, the intervention and control arm patients will continue with follow-up care as the clinician advises and is available to the local service.

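### After baseline the two arms get the outcome booklet by different default routes and at different distances from clinical contact, so the 9-month quality-of-life effect size mixes treatment with collection procedure

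*Protocol article*

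**What the plan says.** At baseline both arms complete the booklet at the 3-month appointment, before randomisation, with help from the research nurse or CNS (Standard care; Nurse-led intervention).

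After randomisation the procedures differ:

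- **Control arm (Standard care).** "Patients will then be asked to complete the same set of outcome measures at the end of each of their follow-up appointments". These are the doctor-led hospital reviews at 6 and 9 months. There is a fallback: "If this is not possible, then the research nurse will send the questionnaires by post for completion and return in a self-addressed, pre-stamped envelope".
- **Intervention arm (Nurse-led intervention).** For the first follow-up booklet, "Patients will receive the same set of outcome questionnaires by post at 6 months post-treatment". The endpoint booklet is posted too, and its timing is given as "within a week of their 9-month telephone follow-up and will be asked to return them in a self-addressed, pre-stamped envelope". No in-person route is given, because these patients do not attend routine hospital follow-up.
- **Scheduled contact in the intervention arm (same section).** The first call comes early: "Patients will receive a scheduled telephone call within 4 weeks of randomisation". The second falls at the endpoint: "Patients will then receive another scheduled telephone call at 9 months post-treatment". No call is scheduled at 6 months.

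Statistical methods then computes between-group effect sizes from final QLQ-C30 scores at the study endpoint, which is 9 months, and uses them to inform the sample size of the full trial. Health economics describes the completeness of EQ-5D-3L and ICECAP-A in both arms.

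**The concern.** A patient-reported score can depend on where it is given and how soon after a clinical encounter. A woman answering in hospital minutes after a medical review may be reassured or unsettled by it. A woman answering a posted booklet is in another setting and at another distance from her last contact. When these circumstances are tied to allocation, a between-arm difference in scores contains both the effect of the follow-up strategy and the effect of the collection procedure. The planned analysis cannot separate them.

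Two outputs of the study are exposed. The first is the QLQ-C30 effect size at 9 months; learning effect sizes for the future power calculation is the stated secondary aim. The second is by-arm questionnaire completeness, from which the investigators want to learn how well the instruments perform in this population. Controls have two routes to a completed booklet and intervention patients have one, so a gap in completeness could reflect logistics alone. The full trial could also inherit the same asymmetry.

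**Working it through.** **Step 1. The procedures side by side.**

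| Time | Control | Intervention |
|---|---|---|
| Baseline (3 months) | In clinic, assisted, before randomisation | The same |
| 6 months | End of hospital review; post if not possible | Post; no scheduled contact at this time |
| 9 months (endpoint) | End of hospital review; post if not possible | Post, within a week of the nurse call |

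At 6 months the contrast in timing is sharp. Randomisation is at the 3-month review and the first call comes within 4 weeks, so by about month 4. The 6-month booklet therefore arrives about 2 months or more after the last scheduled contact, whereas controls answer on the day of a review. At 9 months the gap is smaller. Controls answer on the day, and intervention patients receive the booklet within a week of the call. That window governs receipt. The completion date is open, and the text does not say whether the booklet comes before or after the call.

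**Step 2. Does the shared baseline protect the comparison?** No. The planned effect size uses final scores. Adjusting for baseline would not help either, because the procedural difference begins after randomisation. Controls who fall back to post cannot supply a clean estimate of the mode effect, since they are the ones for whom clinic completion was not possible.

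**Step 3. Group size.** Inputs from Sample size: about 150 cases, 30% not eligible, 50% acceptance. 150 × 0.70 × 0.50 = 52.5, which agrees with the stated hope of about 50. With 1:1 allocation (Randomisation), this gives about 25 per arm.

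**Step 4. Precision.** SE of a standardised difference ≈ √(2/25) = 0.283. The 95% half-width is 1.96 × 0.283 = 0.55. Missing 9-month booklets would widen it. A shift of 0.1 to 0.2 SD from collection procedure (assumed; the protocol gives no figure) lies well inside this interval.

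**Step 5. What such a shift would do to the planned use (illustration).** Assume a true standardised difference of 0.3, two-sided 5% and 90% power: n per arm = 2(1.960 + 1.282)²/d².

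| Assumed procedural shift (SD) | Apparent d | n per arm |
|---|---|---|
| −0.2 | 0.1 | 2102 |
| −0.1 | 0.2 | 526 |
| 0 | 0.3 | 234 |
| +0.1 | 0.4 | 132 |
| +0.2 | 0.5 | 85 |

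The direction of any shift is not known.

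**Step 6. Completeness (illustration).** Assume 90% return in clinic and 65–75% by post. The gap is 25 × (0.90 − 0.75) = 3.75 to 25 × (0.90 − 0.65) = 6.25, or about 4 to 6 patients of 25, with no difference in willingness. Pooled return would be 77.5–82.5%, far above the 50% criterion. Only much lower assumed rates matter there: 70% and 40% pool to 55%, which passes while the postal arm alone would not.

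**The case against.** The strongest reply has five parts.

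- **Part of the contrast is the intervention.** OPCAT-G removes routine hospital attendance, so a different type and recency of clinical contact belongs to the strategy under test. This stands. No data-collection rule can or should remove it. What can be removed is the added difference in where and by what route the booklet is completed.
- **The analysis is exploratory.** The protocol says it will not give definitive results, and with a standard error near 0.28 the estimate is imprecise anyway. This lowers the severity. It does not void the point, because the estimate is meant to feed the next sample size. Sampling error shows in a confidence interval; a procedural shift does not.
- **The 6-month contrast does not enter the effect size.** Correct: the effect size is taken at 9 months, where the arms are closer in timing.
- **Clinic completion may give better return.** This is plausible and is a real cost of the change in a study of about 50 patients.
- **No size is documented.** Correct: every mode effect and return rate used above is an assumption.

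A reader might also infer more than the text supports. It does not say that staff help controls at follow-up; assistance is stated only for baseline. It does not set interview against self-report, since both arms complete the same booklet. Nor does it leave intervention patients without any contact at 6 months: only scheduled contact is absent, and they are told to ring the CNS with problems.

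**Conclusion.** The point holds in a limited form. Setting, delivery route and time since clinical contact differ systematically by arm after an identical baseline. The 9-month QLQ-C30 effect size and the by-arm EQ-5D-3L and ICECAP-A completeness therefore mix treatment with collection procedure. The existence of the difference is certain from the text. Its size and direction are unknown, and with about 25 per arm an assumed shift of 0.1 to 0.2 SD could not be separated from treatment.

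A reader might go further and say that the primary attrition outcome is confounded with treatment. The protocol does not support that. Attrition is counted from consent to completion of any measure, which read literally could be met by the baseline booklet, collected alike in both arms. Retention is judged as a rate against 50%, with no between-arm test. Only if retention means returned follow-up booklets does the route bear on it, and then the pooled decision changes only at low return rates.

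Severity is minor to moderate, because the quality-of-life analysis is exploratory. It is a cheap improvement.

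**What to change.** Use one follow-up procedure in both arms:

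- Post the booklet to every participant at 6 months post-treatment, and within the same window (for example one week) after the 9-month visit or call, with pre-paid return and the same reminder.
- Keep any fallback route identical in both arms.
- Record the completion date and mode for each booklet.
- Report return and completion rates by arm.

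The postal route with a stamped return envelope already exists in the protocol for both arms, so the cost is some postage and a change of procedure. The downside is a control return that may be lower than with completion in clinic. The difference in clinical contact that belongs to the intervention will remain and should be acknowledged when the effect size is interpreted.

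If in-clinic completion is kept for controls, the least that should be done is to record date and mode, report by arm and mode, and state the limitation wherever the effect size is used to plan the full trial.
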